# Research on advanced intervention using novel bone marrOW stem cell (RAINBOW): a study protocol for a phase I, open-label, uncontrolled, dose-response trial of autologous bone marrow stromal cell transplantation in patients with acute ischemic stroke

**DOI:** 10.1186/s12883-017-0955-6

**Published:** 2017-09-08

**Keywords:** Acute ischemic stroke, Bone marrow stromal cells, Cell therapy, Regenerative medicine, Intraparenchymal injection, Platelet lysate, Bio-imaging

## Abstract

**Background:**

Stroke is a leading cause of death and disability, and despite intensive research, few treatment options exist. However, a recent breakthrough in cell therapy is expected to reverse the neurological sequelae of stroke. Although some pioneer studies on the use of cell therapy for treating stroke have been reported, certain problems remain unsolved. Recent studies have demonstrated that bone marrow stromal cells (BMSCs) have therapeutic potential against stroke. We investigated the use of autologous BMSC transplantation as a next-generation cell therapy for treating stroke. In this article, we introduce the protocol of a new clinical trial, the Research on Advanced Intervention using Novel Bone marrOW stem cell (RAINBOW).

**Methods/design:**

RAINBOW is a phase 1, open-label, uncontrolled, dose-response study, with the primary aim to determine the safety of the autologous BMSC product HUNS001–01 when administered to patients with acute ischemic stroke. Estimated enrollment is 6–10 patients suffering from moderate to severe neurological deficits. Approximately 50 mL of the bone marrow is extracted from the iliac bone of each patient 15 days or later from the onset. BMSCs are cultured with allogeneic human platelet lysate (PL) as a substitute for fetal calf serum and are labeled with superparamagnetic iron oxide for cell tracking using magnetic resonance imaging (MRI). HUNS001–01 is stereotactically administered around the area of infarction in the subacute phase. Each patient will be administered a dose of 20 or 50 million cells. Neurological scoring, MRI for cell tracking, ^18^F–fuorodeoxyglucose positron emission tomography, and ^123^I–Iomazenil single­photon emission computed tomography will be performed for 1 year after the administration.

**Discussion:**

This is a first-in-human trial for HUNS001–01 to the patients with acute ischemic stroke. We expect that intraparenchymal injection can be a more favorable method for cell delivery to the lesion and improvement of the motor function than intravenous infusion. Moreover, it is expected that the bio-imaging techniques can clarify the therapeutic mechanisms.

**Trial registration:**

The trial was registered at The University Hospital Medical Information Network on February 22, 2017 (UNIN ID: UMIN000026130). The findings of this trial will be disseminated to patients and through peer-reviewed publications and international presentations.

## Background

Since Azizi et al. published the first report on bone marrow stromal cell (BMSC) transplantation in 1998 [1], BMSCs have been considered as a promising cell source for central nervous system (CNS) regeneration. Some well-known advantages of BMSCs are the ease of their harvest, availability of autologous cells, absence of immunological rejection or tumorigenesis, and freedom from ethical problems [2]. Several articles have reported that BMSCs can survive in the host CNS, migrate to the lesion, and elicit neuroprotective effects when transplanted into animal models of CNS disease [3].

BMSCs originate from bone marrow mononuclear cells (BMMNCs). The floating cells are removed from BMMNCs, and only cells adhering to the floor of the flask are cultured for several weeks to obtain BMSCs [4]. A subpopulation of BMSCs, also termed mesenchymal stem cells, can differentiate into bone, cartilage, and fat. Moreover, there are many reports on their potential to differentiate into other lineages, including neural cells, via so-called transdifferentiation. Many researchers have reported how BMSCs could protect injured CNS. At first, their transdifferentiation to neuronal cells, endothelial cells, or pericyte was noticed. On the other hand, it has been known that they can promote neurogenesis, axonal elongation, vasculogenesis, and so on, due to their secretion of some growth factors or cytokines, so-called nursing effect [5, 6].

The first clinical trial using autologous BMSC therapy in patients with stroke was reported in 2005. Bang et al. showed the feasibility and safety of the therapy [7]. They adopted cell culture methods with fetal calf serum (FCS) and intravenous administration in the protocol. Regrettably, they reported no significant neurological recovery using the Barthel Index and modified Rankin Scale. We hypothesized that some unsolved problems regarding clinical application remained, including safety of the cell culture, suitable delivery routes, cell tracking after the transplantation, and monitoring the effects of intervention [8]. We aimed to solve these problems to develop the next generation of BMSC therapy for stroke. We hypothesize that xeno-free cell culture, direct cell administration near the lesion, and bioimaging for the therapeutic effects are indispensable for the next generation of BMSC therapy [8].

We have reported translational research on human BMSC transplantation in animal stroke models. Human BMSCs were cultured with human platelet lysate (hPL) instead of FCS [9, 10]. The cells were injected stereotactically into rat ischemic brains [9, 10]. In advance, the donor cells were labeled with super­paramagnetic iron oxide (SPIO) for cell tracking using magnetic resonance imaging (MRI) [10]. After the transplantation, ^18^F- fluorodeoxyglucose positron emission tomography (FDG-PET) and ^123^I–Iomazenil single­photon emission computed tomography (IMZ­SPECT) were performed to analyze cellular function and metabolism in the host brain [11, 12]. There were no differences in the surface markers and cell proliferation between cells culture in hPL and FCS [9]. Although a rotarod test showed that motor function deteriorated in rats suffering from permanent middle cerebral artery occlusion, a BMSC-hPL transplantation enhanced recovery of the motor function significantly [9]. MRI demonstrated that the SPIO-BMSCs aggressively migrated towards the lesion [10]. Moreover, FDG-PET and IMZ-SPECT showed that BMSC transplantation promoted recovery of the glucose utilization and the binding potential of iomazenil, respectively, in the peri-infarct area [11, 12]. Histological analysis supported the findings on MRI and showed an inclination for neural differentiation of donor cells [10, 13, 14].

We used these results to determine the optimal study design of our new clinical trial, Research on Advanced Intervention using Novel Bone marrOW stem cell (RAINBOW). The trial is a Phase I study to assess the potential benefits of autologous BMSC product (code name: HUNS001–01) administration to patients with acute ischemic stroke. We aim to evaluate its safety, feasibility, and efficacy. Autologous BMSC were cultured with allogeneic PL in the cell processing center (CPC) according to good manufacturing practice (GMP). The cells were labeled with SPIO. They were injected around the infarct stereotactically. After administration, we will perform MRI for cell tracking and FDG-PET and IMZ-SPECT for the analysis of the therapeutic effect. In addition, we hope that this study proves helpful in clarifying the therapeutic mechanisms. In the study, we expect that the findings of SPIO-labeling/MRI will help us to choose the suitable transplant location. About the therapeutic mechanisms, for instance, if MRI showed that the cluster of donor cells moved to SVZ, it might be an evidence for stimulation of endogenous neuronal regeneration. And FDG-PET and IMZ-SPECT may show the relation between the transplant location and the reaction of the host brain, for examples, brain metabolism may be increased in the contralateral hemisphere to the transplant location.

## Methods/design

### Study design

This study is an open-label, uncontrolled, dose-response, single-center, phase I clinical trial. The subjects will receive standard medication for 14 days after the onset of their stroke. The patients are then screened, and bone marrow harvest is performed as soon as possible. The BMSCs are cultured with allogeneic PL, and HUNS001–01 is manufactured from autologous BMSCs in the CPC. Once the preparation of HUNS001–01 is almost complete, the administration date is planned, and a second screening is performed 7 days before the administration. If the subject meets the requirements, HUNS001–01 (cell dose: 2 × 10^7^ or 5 × 10^7^ cells) is injected into the brain stereotactically. Follow-up is done for 1 year after the administration. The detailed trial flow is described in Fig. 1. This study is conducted in the Department of Neurosurgery, Hokkaido University Hospital, Sapporo, Japan. The trial was registered at The University Hospital Medical Information Network on February 22, 2017 (UMIN ID: UMIN000026130). The total study period is approximately 3 years, between March 2017 and August 2020.

**Fig. 1 Fig1:**
[figure not shown]
The detailed trial flow of RAINBOW

### Study population

Inclusion criteria (First screening; 14 days after the onset of stroke).Male or female subjects between 20 and 79 years oldInformed consent within 14 days after the onset of strokeClinical diagnosis of cerebral ischemic stroke in the internal carotid arterial regionSubjects with a modified Rankin Scale (mRS) of 0 or 1 before the onset of strokeSubjects who can give informed consent; if insufficiently able, a legal representative is neededSubjects with moderate or severe neurological symptoms; National Institute of Health Stroke Scale (NIHSS) ≥ 6, (however, the partial score in both “Motor Arm” and “Motor Leg” must be ≥6)

(Second screening; 7 days before the administration of HUNS001–01).HUNS001–01 must be available within 74 days after the onsetSubjects with moderate or severe neurological deficit; mRS ≥ 3

Exclusion criteria (First screening; 14 days after the onset of stroke)Occurrence of severe hemorrhagic transformation of ischemic strokeSubjects in a coma or a deep coma with a JCS-200 or JCS-300 score evaluated by the Japan Coma ScaleSevere anemia (hemoglobin < 10.0 g/dL) or thrombocytopenia (platelet count < 100,000/mm^3^)Severe heart disease (e.g., ischemic heart disease, heart failure)Significant abnormalities in laboratory tests:a. >3 × upper limit of normal (ULN) for alanine aminotransferase or aspartate aminotransferase.b. >1.5 × ULN for total bilirubin.c. >1.5 × ULN for serum creatinineUncontrolled hypertension, despite antihypertensive therapyHistory of malignancy of any typeCarriers of any of the following infectious diseases: Syphilis, hepatitis B virus (HBV), hepatitis C virus (HCV), human immunodeficiency virus (HIV)-1/2, human T cell leukemia virus (HTLV)-1, or parvovirus B19Subjects who are pregnant or want to have childrenHistory of seizure or administration of any antiepileptic drugsContraindication for fosphenytoin sodium hydrate (Fostoin®, Eisai Co., Ltd., Tokyo, Japan)Serious allergy to any possible residues in the test product (e.g., any biomaterials used in manufacturing process, gentamicin sulfate, ferucarbotran) or any agents used for the administration of the test product or for inspections during the trialContraindication for MRI (e.g., a pacemaker, metallic artificial heart valves, an implantable cardioverter defibrillator)Subjects who are inappropriate for this trial based on the judgment of the primary investigator or other investigators; for example, if other intracranial disorders were diagnosed due to history, symptoms, or neuroradiological findings during the trial, the primary investigator or other investigators will make a decision after reviewing the risks and benefits.

(Second screening; 7 days before the administration)Occurrence of severe hemorrhagic transformation of ischemic strokeSubjects in a coma or a deep coma with a JCS-200 or JCS-300 score evaluated by Japan Coma ScaleSevere anemia (hemoglobin < 10.0 g/dL) or thrombocytopenia (platelet count < 100,000/mm^3^)Severe heart disease (e.g., ischemic heart disease, heart failure)Significant abnormal laboratory tests:a. >3 × ULN for alanine aminotransferase or aspartate aminotransferase.b. >1.5 × ULN for total bilirubin.c. >1.5 × ULN for serum creatinineUncontrolled hypertension, despite antihypertensive therapySubjects who are inappropriate for this trial based on the judgment of the primary investigator or other investigators; for example, if other intracranial disorders were diagnosed due to history, symptoms, or neuroradiological findings during the trial, the primary investigator or other investigators will make a decision after reviewing the risks and benefits.

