### Intervention

On the day when HUNS001–01 is manufactured, the cell product will be administered to the subject. A dose of 2 × 10^7^ cells (400 μL) will be administered in the low-dose group and a dose of 5 × 10^7^ cells (1000 μL) will be administered in the high-dose group. HUNS001–01 is implanted using MRI stereotactic technique to define the target sites in the normal white matter around the lesion. The number of target sites is one or two in the low-dose group, and two or three in the high-dose group. The subject has a one or two burr-hole craniotomy under local anesthesia and sedation. Using 2.1-mm outer diameter stereotactic cannula, 200 to 500 μL of the product is injected over a period of 5 min at each site. The cannula is removed after 5 min after finishing the injection at each site. In the perioperative period, all subjects take fosphenytoin sodium hydrate to prevent epileptic seizure due to the procedure.

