### Follow-up of study

The schedule of follow-up of study is as follows (Table 1):Vital signs, serological, and biochemical tests: Days 0, 1, 3, 7, 14, 30, 90, 180, 360Urinalysis: Days 30, 90, 180, 360Urine hCG-β (if needed): Days 90, 180, 36012-lead electrocardiogram and chest X-ray examination: Days 1, 7, 30, 90, 360Neurological examination (NIHSS, mRS, FIM, Barthel Index, Fugl-Meyer Assessment): Days 1, 3, 7, 14, 30, 90, 180, 360MRI: Days 0, 3, 7, 14, 30, 90, 180, 360FDG-PET and IMZ-SPECT: Days 30, 90, 360

**Table 1 Tab1:** The schedule of follow-up of study

	Screening			Follow up									
	1st screening	BM hervest	2nd screening	Pre-administration	Post-administration								
	Onset to14 days		Day −7 (±1)	Day 0		Day 1	Day 3	Day 7	Day 14	Day 30 (±3)	Day 90 (±30)	Day 180 (±30)	Day 360 (±30)
Informed consent	X												
Medical history	X												
Vital signs	X	X	X	X	X	X	X	X	X	X	X	X	X
Body weight and height	X												
Serological tests	X		X		X	X	X	X	X	X	X	X	X
Biochemical tests	X		X		X	X	X	X	X	X	X	X	X
Urinalysis	X		X							X	X	X	X
Urine hCG-β (If needed)	X									X	X	X	X
Infectious disease inspection	X												
12-lead electrocardiogram	X		X			X		X		X	X		X
Chest X-ray examination	X		X			X		X		X	X		X
Neurological examination	X		X			X		X		X	X	X	X
MRI	X		X	X	X		X	X	X	X	X	X	X
FDG-PET and IMZ-SPECT			X							X	X		X
Bone marrow harvest		X											
Cell product administration				X									
Concomitant medication	X	X	X	X	X	X	X	X	X	X	X	X	X
Adverse events	X	X	X	X	X	X	X	X	X	X	X	X	X

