## Discussion

### Subject screening

Current therapeutic strategies for ischemic stroke typically aim to improve blood flow in ischemic areas or to relieve neuronal damage through neuroprotective effects before the ischemic disorder is established. However, in cell therapy, some strategies aim to resolve neurological disorders resulting from an established cerebral infarction. Autologous cell products, in particular, require time for tissue collection and manufacturing. If changes in a subject’s condition are anticipated during the manufacturing period, appropriate screening at the start of the administration, as well as at the enrollment should be established.

In our trial, NIHSS score is assessed in the first screening on day 14 after the onset. The NIHSS is used for systematic assessment of potential symptoms and signs of stroke, and is designed primarily to assess symptoms and signs in the acute phase and to determine the severity of the disease. On the other hand, mRS, which is one of the disability measures, has been widely used as an efficacy endpoint in clinical trials all over the world. In our trial, mRS is examined in the second screening, 7 days before the administration. H, the NIHSS score on admission is inadequate for the first screening. Due to the weak correlation with the mRS score in chronic phase, possible dropouts are expected at the second screening. In fact, Kimura et al. reported that approximately half of the subjects with NIHSS scores of 7–10 at admission would have an mRS score of 0–2 at discharge [16]. We adopted the NIHSS on day 14 after the onset, but not on admission, as the first screening, because it has a stronger correlation with the mRS score and other outcome scales in the chronic phase [17].

In the trial, we enrolled patients who met the inclusion criteria of a total score of NIHSS ≥6, and a “Motor Arm” and “Motor Leg” score of NIHSS ≥6 at the first screening, since the improvement of injured motor function is an anticipated result of the administration of HUNS001–01.

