### Time point of cell administration

In the protocol, we cannot provide the exact time point of cell administration. The autologous cells need a period for cell culture before the administration. We expect that the range of the period will be from 2 to 5 weeks, and then we will administer the cells as soon as possible. But the period may be prolonged due to some factors, for examples, aging of subjects. We set the dead line of the administration to 74 days after stroke onset, which means the culture period is set for maximum 60 days, because delayed cell administration may miss the therapeutic time window and the cells with too slow growth may be unhealthy or ineffective.

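### No repeat pregnancy test or exclusion is scheduled between the first screening and dosing, so the second-screening radiotracer scans and the surgery rest on the first-screening check alone

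*Protocol article*

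**What the plan says.** Under Study population, the article prints two separate exclusion lists. The first is headed "Exclusion criteria (First screening; 14 days after the onset of stroke", and it excludes subjects who are pregnant or who want children. The second is headed "Second screening; 7 days before the administration". It repeats hemorrhagic transformation, coma, anemia and thrombocytopenia, heart disease, laboratory limits, uncontrolled hypertension and the investigator's judgment. It does not repeat pregnancy. Women are eligible from age 20.

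Under Follow-up of study, the Table 1 row "Urine hCG-β (If needed") is marked at the first screening and on days 30, 90, 180 and 360. It is blank at marrow harvest, second screening and day 0. The text above the table lists hCG on days 90, 180 and 360 only. Table 1 places FDG-PET and IMZ-SPECT at the second screening and on days 30, 90 and 360.

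Under Intervention, the day-0 procedure is described in these words: "The subject has a one or two burr-hole craniotomy under local anesthesia and sedation". The same section states that "all subjects take fosphenytoin sodium hydrate to prevent epileptic seizure due to the procedure".

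**The concern.** The second screening exists because a subject's condition can change while the cells are grown. The Discussion (Subject screening) makes this argument itself: where change is expected during manufacturing, subjects should be screened at administration as well as at enrollment. Pregnancy status can change over that period, and scheduling hCG at four visits after dosing shows that the sponsor treats it as changeable. Yet the visit that clears a subject for the scans and the operation neither lists pregnancy nor tests for it.

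This is a matter of patient safety and affects no endpoint or analysis. A woman who conceives after the first screening, or whose pregnancy was too early to detect then, could receive two radiotracers, fosphenytoin, sedation and stereotactic brain surgery with no further scheduled test.

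**Working it through.** **Reading Table 1 by column**

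| Row | Visits marked |
|---|---|
| Urine hCG (if needed) | first screening, days 30, 90, 180, 360 |
| Urinalysis | first screening, second screening, days 30, 90, 180, 360 |
| FDG-PET and IMZ-SPECT | second screening, days 30, 90, 360 |

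The hCG and urinalysis rows match except at the second screening. In Table 1 the second screening is also the only radiotracer visit without an hCG mark.

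**Inputs for the intervals**

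- First screening on day 14. The Discussion (Subject screening) says "NIHSS score is assessed in the first screening on day 14 after the onset". Table 1 heads this visit as running from onset to 14 days, so day 14 is the latest date.
- Marrow harvest on day 15, the earliest date allowed by the Abstract ("15 days or later from the onset").
- Culture period, from Time point of cell administration: "We expect that the range of the period will be from 2 to 5 weeks". This is an expectation, not a limit.
- Dosing deadline of day 74 after onset (Study population; Time point of cell administration).
- Second screening 7 days before dosing, with a window of ±1 day (Table 1).

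**The plan's own figure.** The article gives a maximum culture period of 60 days. This reproduces as 74 − 14 = 60, counted from day 14.

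**Formulas**

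- Dosing day = 15 + culture days, capped at 74.
- Gap to scans = (dosing day − 7) − 14.
- Gap to dosing = dosing day − 14.
- Gap to next scheduled hCG = dosing day + 30 − 14 by Table 1, or dosing day + 90 − 14 by the text.

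| Case | Dosing day | Gap to scans | Gap to dosing | Next hCG, Table 1 | Next hCG, text |
|---|---|---|---|---|---|
| 2-week culture | 15 + 14 = 29 | 22 − 14 = 8 | 29 − 14 = 15 | 59 − 14 = 45 | 119 − 14 = 105 |
| 5-week culture | 15 + 35 = 50 | 43 − 14 = 29 | 50 − 14 = 36 | 80 − 14 = 66 | 140 − 14 = 126 |
| Deadline | 74 | 67 − 14 = 53 | 74 − 14 = 60 | 104 − 14 = 90 | 164 − 14 = 150 |

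All gaps are in days.

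**Sensitivity**

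- The ±1 day window widens the range to the scans from 8–53 days to 7–54 days.
- With first screening on day 7, the deadline case becomes 67 − 7 = 60 days to the scans and 74 − 7 = 67 days to dosing.
- With first screening on day 1, it becomes 67 − 1 = 66 and 74 − 1 = 73 days.

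**The case against.** The strongest case on the other side is that little exposure remains. Enrollment is 6 to 10 patients aged 20 to 79, all with a marked motor deficit at the first screening and mRS of at least 3 at the second. Anyone wanting children is already excluded, and the test applies only if needed. The article does not say how many subjects would need it. All of this stands and sets the severity, but it does not exclude an unintended or very early pregnancy.

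A second argument is that an article condenses the full protocol, and that a check before imaging or surgery may sit there or in hospital procedures. That limits any claim about what happens in practice. It does not remove the point, because the article prints both the second-screening list and the full visit schedule, and the schedule places hCG at other visits.

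A third is that the second-screening list lets the investigator exclude any unsuitable subject. That covers a known pregnancy but triggers no test.

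A reader might infer three stronger things that the documents do not support:

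- *That pregnancy goes untested before exposure, or is never rechecked.* The first-screening test precedes the scans and dosing, and hCG is scheduled again afterwards. What is missing is a repeat in between.
- *That a pregnancy would first come to light on day 30 or day 90.* Those are only the next scheduled tests. Adverse events and concomitant medication are recorded at harvest, second screening and day 0, so a pregnancy could be recognized sooner.
- *That the fosphenytoin contraindication, and seizure or antiepileptic use since enrollment, must also be carried forward.* Those same records and the investigator's discretion already cover them.

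The day-30 difference between text and table is a separate editorial slip. The text lists follow-up visits only, so it is no evidence about testing before dosing.

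**Conclusion.** The point holds as a minor safety gap. The plan as printed neither repeats the pregnancy exclusion at the second screening nor schedules a repeat hCG before the radiotracer scans, fosphenytoin and surgery.

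The gap since the last scheduled test is about 8 to 53 days at the scans and 15 to 60 days at dosing. These are not protocol limits. The lower ends assume first screening on day 14, harvest on day 15 and the expected 2-week culture. The upper ends assume first screening on day 14 and dosing at the day-74 deadline, and they grow if the first screening is earlier. Confidence is high about what the printed list and schedule contain. The documents cannot show whether local practice adds a check.

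**What to change.** Make three changes:

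1. Add pregnancy to the second-screening exclusion list in Study population.
2. In Table 1, mark urine hCG (if needed) at the second screening, and require the result before FDG-PET and IMZ-SPECT.
3. Add day 30 to the hCG entry in the Follow-up of study text, so that it agrees with Table 1.

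The interval since the last test then falls to 0 days at the scans, if the test is done the same day, and to 7 (±1) days at dosing.

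The cost is one urine test on urine already collected for urinalysis at that visit, one line of eligibility wording, one table mark and one text correction. The downside is that an occasional patient would be lost after marrow harvest.
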